### Speech target selection

Children with CLP may present with multiple CSCs affecting intelligibility. We intend to select as intervention targets speech sounds which are (1) amenable to treatment with both interventions and (2) likely to have the biggest functional impact on intelligibility, based on the prevalence of the error during assessment and how frequently the target sound occurs in English minimal pairs [20]. Following the screening assessments, we will select wordlists targeting each child’s specific lingual errors from a battery. In English, lingual speech sounds (imageable with ultrasound and amenable to treatment with both interventions) are /t,d,n,r,l,s,z,∫,ʒ,tʃ,dʒ,j,k,ɡ,ŋ/ and all vowels. Children with CLP are more likely to have difficulty with anterior consonants /t,d,s/. Wordlists containing these speech sounds will also form a key outcome measure (see below). Two wordlists per error type will be selected, firstly an “untreated probe” (i.e., the words will not be used in the course of therapy, and this allows us to check for generalization of targets). Secondly a “treated probe”, containing high-frequency and functionally useful words will be used to train speech targets in the course of therapy. The wordlists contain lingual targets in increasingly complex contexts from single syllable words/pseudowords through to multi-syllabic words and sentences. Where the child has more than one error, multiple wordlists will be used; however, only one treatment target (the speech sound with the most errors) will be selected and the other errors will serve as “control segments” (i.e., speech sounds that should not improve during the course of therapy unless maturation is a factor). Wordlists will be analyzed for percentage target consonants correct (PTC). Children must score < 30PTC at baseline to be eligible for the study.

### Interventions

Both interventions will be delivered by the cleft palate specialist SLTs in the Royal Hospital for Children in Glasgow. Therapy in both treatment arms will be once per week for six sessions with each session lasting up to 45 min. The number of sessions is pragmatic in nature, reflecting current practice, and is designed to highlight initial response to both interventions. It is likely that some children in both arms of the trial may require further speech intervention in the future (after the follow-up measures are taken), and this will be provided in line with standard practice, which includes further U-VBF. Both interventions will focus on acquisition of new speech sounds. Previous studies of children with non-cleft speech disorders show that a new speech sound can be acquired within one to two sessions [21] of U-VBF for most children but that some children take four to six sessions. Target articulations will be decided individually. Both interventions begin with a pre-practice phase where the aim is to teach the child to approximate the target articulation before they can begin the practice phase where at least 100 repetitions are required for learning and generalization. The dosage of a minimum of 100 trials is set in line with [22] who report a minimum of 60 to 120 trials per session for motor-based treatments. However, we recognize that the literature on dosage required during intervention for CSCs is sparse and that there is much variation reported in the literature on articulation intervention [23]. This dosage will be measured in both interventions. In this pilot we will focus on both the pre-practice phase and the first stage of practice: acquisition of a new sound in simple contexts such as “ta, tea, toe” building to short words such as “tap, team, tore” as this is feasible within six intervention sessions. If children are super-responders (i.e., they quickly retain the new speech sound and are able to produce it in complex contexts) then the protocol will also allow us to measure this. Participants will be discontinued from the intervention if they show any adverse effects to the ultrasound treatment—in rare cases, the ultrasound gel can cause contact dermatitis [24].

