#### Objectives

To determine recruitment and attrition rates.75% of children and their families identified agree to participate.75% of children allocated in each group are retained for the duration of the study.To measure pre-post and follow-up outcome measure completion.75% of outcome measures are completed.To measure within-session outcome measure completion.Data is reported from 75% of intervention sessions.To determine acceptability of randomization to children and their families.75% of children and their families rate randomization as acceptable in a questionnaire.To determine the acceptability of ultrasound visual biofeedback as an assessment tool (both groups) and intervention tool (U-VBF group).75% of children and their families rate ultrasound as an acceptable technique in a questionnaire.Focus group analysis contains more positive than negative themes regarding acceptabilityTo measure adherence to the treatment protocol.75% of sessions reach the minimum dosage of 100 trials in both treatment arms.

In addition to the quantitative objectives measuring acceptability using questionnaires, this data will be validated using focus group interviews with parents and participants who volunteer. The interviews will be analyzed inductively to identify emergent themes and deductively, using the Theoretical Framework of Acceptability [14].

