### Eligibility/baseline assessments

We will screen potential participants from case-notes and invite them to attend an initial screening and baseline assessment. The person carrying it out will obtain consent, ensuring the participants and their families have had time to read, understand, and discuss the information about the study, prior to any assessment or procedures. The person carrying out this assessment will not be involved in the therapy. This assessment will be either in person or via video conferencing, with in-person preferred. Screening assessment will comprise the British Picture Vocabulary Test 3 [15] to screen for adequate receptive vocabulary. This test does not require verbal responses or assess speech production, instead participants point to responses. The screening will also include a speech assessment protocol to determine whether patients present with at least one cleft speech characteristic which would be amenable to both U-VBF and the control intervention. This assessment protocol comprises the Diagnostic Evaluation of Articulation and Phonology [16] articulation and phonology subtests and an ultrasound tongue imaging protocol designed in a previous project [11] to identify covert speech errors from consonants at all places of articulation and sentences from the GoS.SP.aSS.’98/ CAPS-A [17] (Appendix 1). Families who opt for the assessment over video-conferencing will complete the same assessments, but the ultrasound tongue imaging protocol will be replaced with an audio-perceptual assessment of the same materials^1^.

There are some limitations that may arise as a result of online video assessment, such as detecting sounds where the articulators are not visible (e.g., /k/ or /g/) or detecting high-frequency sounds (e.g., /s/ or /ʃ/), despite overall good agreement rates reported for online articulation assessments [18]. However, we retain this option for participants to address potential national and local pandemic regulations [19] during which travelling to a university for assessment is not classified as essential travel.

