### Candidate primary outcome measures

The key primary outcome linear measure for change in speech will be percentage target consonants correct (PTC). We will measure this at single sound level (stimulability and in /aCa/ contexts); single word level; and sentence level in treated and untreated wordlists (i.e., probes, see above section on speech target selection). All direct speech measures will be recorded with audio and where possible ultrasound tongue imaging in both groups, allowing us to perform ultrasound analysis of data from both groups.

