### Ultrasound/speech analysis

All of the speech measures at baseline, and follow-up will be recorded with simultaneous ultrasound in both groups by a research SLT blinded to group where possible. Our previous work showed that the addition of ultrasound to transcription increases inter-rater reliability and allows identification of covert (imperceptible to the ear alone) errors [9]. This will allow us both to calculate PTC (the primary outcome measure) with increased reliability and to perform an error analysis. Twenty-five percent of the data will also be rated by two specialist cleft SLTs (not involved in the project) trained in ultrasound-aided transcription. These SLTs will also rate the audio recordings from the within-treatment sessions (t1 to t6 in Table 1), blinded to group.

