### Harms

Based on previous studies using ultrasound intervention for speech sound disorders, no harm to the participants is anticipated. In rare cases, some people may have an allergic reaction (contact dermatitis) to the gel [24]. If this is observed, the gel can be substituted with water. If water does not achieve a sufficiently good ultrasound image, then the participant may be discontinued from the trial. If any adverse consequences are observed, they will be recorded in the participant’s clinical notes and reported to the NHS ethics committee using standard procedures. The ethics committee and the university ethics committee can audit the trial at any time. The study has been granted ethics approval by the West Midlands-South Birmingham Research Ethics Committee, reference number 21/WM/0104.

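### Two sections give incompatible instructions for a child who reacts to ultrasound gel, and one does not separate stopping ultrasound from leaving the trial

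*Protocol article*

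**What the plan says.** The Interventions section of the protocol article ends with a discontinuation rule: "Participants will be discontinued from the intervention if they show any adverse effects to the ultrasound treatment". It illustrates the rule with the remark that "in rare cases, the ultrasound gel can cause contact dermatitis".

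The Harms section returns to contact dermatitis from the gel and gives two steps. First: "If this is observed, the gel can be substituted with water". Then: "If water does not achieve a sufficiently good ultrasound image, then the participant may be discontinued from the trial".

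On outcomes, the section on candidate primary outcome measures says "All direct speech measures will be recorded with audio and where possible ultrasound tongue imaging in both groups". The Ultrasound/speech analysis section says the speech measures at baseline and follow-up "will be recorded with simultaneous ultrasound in both groups by a research SLT blinded to group where possible". The Outcome measures section places assessments at baseline, at 2 months after randomization (t7) and at 3 months (t8), in a university clinic or by video-conferencing. For families who choose remote screening and baseline assessment, "the ultrasound tongue imaging protocol will be replaced with an audio-perceptual assessment of the same materials".

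One of the success criteria under Objectives is that "75% of children allocated in each group are retained for the duration of the study". Another asks for 75% completion of outcome measures. The target is 20 children per arm.

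**The concern.** There are two linked problems.

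First, a safety instruction in a trial of children should read one way. A therapist who sees dermatitis partway through the six sessions must stop the intervention under one section and can continue with water under the other. Both cannot be followed.

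Second, the sections stop different things: one ends the intervention, the other may end trial participation. On its natural reading, leaving the trial ends the t7 and t8 assessments, although the article does not spell this out. The stated ground, an inadequate ultrasound image, does not prevent those assessments. A child who could have been assessed may therefore be recorded as lost, which counts against the retention and completion criteria that this pilot exists to measure. The Background says a full-scale trial would follow a similar design if the criteria are met, so unclear wording could carry over into it.

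**Working it through.** No stated sample size, power or error rate is in dispute, so there is no figure to reproduce. The check is mainly a comparison of texts.

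**The two rules side by side**

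| | Interventions | Harms |
|---|---|---|
| Event | Any adverse effect of the ultrasound treatment; gel dermatitis is the example | Gel dermatitis |
| Trigger for discontinuing | The adverse effect itself | Inadequate image after changing to water |
| Force | Mandatory | Permissive |
| What is stopped | The intervention | The trial |

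They differ on the last three rows for the same event. Reading the Interventions sentence as a summary of Harms does not resolve this, because a mandatory rule covering every adverse effect leaves no room for a substitution step.

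**Whether t7 and t8 outcomes need ultrasound**

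- PTC: recorded by audio, with ultrasound only where possible.
- Mode: video-conferencing is allowed after treatment (Outcome measures). An audio-perceptual replacement is already written for remote screening and baseline.
- Intelligibility in Context Scale (carer-reported) and CLEFT-Q (age 8 and over): rating scales.

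None of these depends on an adequate ultrasound image.

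**Exposure by arm**

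Ultrasound is used at assessments in both arms where possible. If every assessment is in person, a control child has 2 ultrasound occasions after randomization (t7, t8) and a U-VBF child has 6 + 2 = 8. Baseline exposure comes before randomization and is common to both arms. Exposure is greater in U-VBF but not confined to it.

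**Size against the retention criterion**

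- One child: 1/20 = 5 percentage points of one arm's retention.
- Needed: 0.75 × 20 = 15 retained, so 20 − 15 = 5 losses are tolerated and the sixth fails the criterion.

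The article gives no reaction rate. For scale only, let *b* be assumed retention from all other causes and *q* the assumed chance that a U-VBF child leaves the trial because of a gel reaction, with children independent. The chance that the arm meets its criterion is P(X ≥ 15), where X ~ Binomial(20, *b*(1 − *q*)):

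| *b* | *q* = 0 | *q* = 1% | *q* = 2% | *q* = 5% |
|---|---|---|---|---|
| 90% | 0.989 | 0.983 | 0.976 | 0.941 |
| 85% | 0.933 | 0.916 | 0.897 | 0.828 |
| 80% | 0.804 | 0.777 | 0.749 | 0.657 |

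The *q* = 0 column is also the result if children who stop ultrasound stay in follow-up. At *q* of 1% to 2% the chance falls by between 0.6 points (0.989 − 0.983) and 5.5 points (0.804 − 0.749). The expected number of such losses is 20*q*: 0.2 at 1%, 0.4 at 2% and 1.0 at 5%. The chance of at least one is 1 − (1 − *q*)^20: 18%, 33% and 64%.

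**The case against.** The strongest reply is that this is a wording difference about a rare event in a condensed article, and that Harms may simply hold the operational detail. That softens the conflict but does not remove it, because the article prints both instructions and they direct different actions.

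A reader might also infer that the plan removes reacting children from the trial and so builds avoidable, treatment-related missing outcomes into the U-VBF arm. The documents do not support that reading:

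- Withdrawal under Harms needs a rare reaction, then failure of water, then a discretionary decision.
- Gel is also used at assessments in both arms, including before randomization, and Harms is not limited to one arm.
- One such child cannot fail the retention criterion alone.
- Families of children who drop out are still offered the acceptability questionnaire, so not all data are lost.
- No definitive comparison of the interventions is planned, so no confirmatory treatment effect can be biased.

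These points stand and limit the concern to the contradiction and the missing separation between stopping ultrasound and leaving the trial.

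It is also fair to say that audio-only PTC is not equivalent to ultrasound-aided PTC. The Ultrasound/speech analysis section reports better inter-rater reliability with ultrasound and detection of covert errors. But the plan already accepts assessment without ultrasound, and a less reliable measurement is more useful than none.

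Finally, how such a child is handled in the analysis is commonly left to the statistical analysis plan, so its absence here is not criticised.

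**Conclusion.** The point holds in a limited form. The Interventions and Harms sections contradict each other on trigger, force and what is stopped for the same gel reaction, and they must be reconciled. This rests on the text alone and needs no assumption about rates.

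The second part also holds: Harms permits withdrawal from the trial on a ground that does not prevent outcome collection. It assumes the ordinary meaning of leaving a trial, namely that t7 and t8 assessments cease.

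The numerical effect is small. Each affected child is 5 percentage points of one arm's retention, with 5 losses tolerated. The fall of 0.6 to 5.5 points in the chance of meeting the criterion depends on removal rates of 1% to 2% and other-cause retention of 80% to 90%, all of them assumptions. The reason to act is a safety instruction that reads two ways and a correction that costs almost nothing, rather than any large effect on the pilot's results.

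**What to change.** 1. The clinical team should reconcile the Interventions and Harms sections into one rule that states the trigger, whether action is mandatory or discretionary, and what is stopped. No clinical rule is proposed here.
2. In Harms, separate stopping ultrasound from leaving the trial. State that neither an inadequate image nor stopping ultrasound treatment by itself ends t7 and t8 outcome collection. Subject to continued consent, the child is assessed with audio-recorded speech measures (in person or by video-conferencing) and the applicable rating scales.
3. State that a child assessed in this way counts towards the retention and outcome completion criteria under Objectives.

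The cost is wording in two paragraphs, reported to the registry and the ethics committee as the article already provides for protocol changes. No new assessments are needed. The drawback is somewhat less reliable PTC for the few children assessed without ultrasound, so the mode of assessment should be recorded.

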### Articulation intervention (AI)

This intervention involves working on a single speech sound at a time [23]. The SLT uses modelling, demonstration, verbal description, and feedback in the pre-practice phase to teach the child the new sound at first in limited contexts and then in words and finally in conversation in the practice phase. To increase parity with U-VBF, and in line with newer theories of motor learning [25], we will standardize the in-session dosage during the practice phase to at least 100 trials, i.e., each child will be given 100 attempts to articulate their target articulation in each session.

### Ultrasound visual biofeedback (U-VBF)

This intervention is grounded in the principles of motor learning. The patient sees a real-time image of their tongue moving (see [9] for a video) and guided by the SLT uses this biofeedback to learn a new articulation, building productions to increasingly complex contexts, as in AI. Again, a minimum of 100 trials are required in the intervention. The intervention is set out in an open access manual [26] and involves using the software Sonospeech^TM^. The software has functionality to be used as an assessment and intervention tool, allowing the SLT and patient to record and playback ultrasound video with synchronized audio or to view it live. The clinicians delivering the intervention have completed training and currently use ultrasound in their clinical practice.

### Outcome measures

A blinded assessor will collect measures at baseline (-t1: pre-treatment), 2 months post-randomization (t7, to allow for any delays in referral to therapy), and 3 months post-randomization (t8) to see if any benefit is maintained. Assessment will take place in a university clinic or via video-conferencing and will be carried out by a research SLT blinded to group for primary outcome measures and by the treating SLTs for within-session measures (Table 1).

**Table 1 Tab1:**
[figure not shown]
Shows the timeline for the project, including the timing of each assessment

### Within-treatment session outcomes

Previous research suggests that one of the main benefits of U-VBF may be efficiency rather than overall efficacy of treatment [8]. We will therefore measure treatment response during each session, rather than just after the course of treatment. The treating SLTs will therefore audio record short treated, and untreated word lists at every treatment session (t1–t6). From this, we will determine how quickly children achieve a new articulation as a measure of response to treatment. These will be rated at the end of the project by SLTs blinded to group.

### Candidate primary outcome measures

The key primary outcome linear measure for change in speech will be percentage target consonants correct (PTC). We will measure this at single sound level (stimulability and in /aCa/ contexts); single word level; and sentence level in treated and untreated wordlists (i.e., probes, see above section on speech target selection). All direct speech measures will be recorded with audio and where possible ultrasound tongue imaging in both groups, allowing us to perform ultrasound analysis of data from both groups.

### Patient reported outcome measures

We will use the Intelligibility in Context Scale [27] as a carer reported outcome. This short scale asks parents/carers to rate how easy to understand their child is to a variety of listeners ranging from family members to strangers. It has been shown to have a high internal reliability and construct validity [27]. Quality of life will be measured using the CLEFT-Q speech function and quality of life scales for children aged 8 and over [28]. This instrument has good content and construct validity, and good reliability, as established using a large and diverse international sample of participants [28]. We will also use the Experience of Service Questionnaire [29] to measure patient and carer satisfaction with both interventions at the end of the project. It was shown to have good construct validity and precision in measuring satisfaction with care [29]. The bespoke data collection forms, such as the participant information sheets and the consent form templates, can be found in a publicly accessible folder on the University of Strathclyde open access Knowledge Base “PURE” [30] (or via DOI 10.15129/f65343c4-7781-44fe-9b00-516d4597efac).

### Intervention acceptability measures and qualitative evaluation

Families will complete a questionnaire about the acceptability of both interventions at the end of the study. These questionnaires will also be offered to families of participants who drop out of the study. Participant retention will be promoted by dedicating time to discuss any questions and problems that may have arisen for the participant and their family at the start of each session and by offering further ultrasound or articulation intervention after the final follow-up if indicated. Parents/carers and children over 12 will be invited to join focus groups to discuss their experiences of taking part in the trial and to contribute to planning a larger trial. Focus groups will be run by the PI and an RA online using the topic guide available in a publically accessible folder available at [30] (or via DOI 10.15129/f65343c4-7781-44fe-9b00-516d4597efac). Each focus group will include up to 10 participants. Responses to the focus groups will be analyzed by an RA using thematic analysis, following the same methods employed in a similar study with children with cerebral palsy [31], that is, inductive thematic analysis.

